**Methods:**

ICAT-COVID is a multicenter, randomized, open-label, proof-of-concept phase II clinical trial assessing the clinical efficacy and safety of adding icatibant to the standard of care in patients hospitalized with COVID-19 without invasive mechanical ventilation. Patients hospitalized with a confirmed COVID-19 pneumonia diagnosis (RT-PCR or antigen test ≤ 10 days prior to randomization, and radiographic evidence of pulmonary infiltrates), rated “4” or “5” on the WHO’s clinical status scale, are eligible. Patients will be randomized on a 1:1 ratio to either standard of care-plus-icatibant (experimental group) or to standard of care alone (control group). The experimental group will receive 30 mg of icatibant subcutaneously 3 times a day for 3 days (for a total of 9 doses). The expected sample size is 120 patients (60 per group) from 2 sites in Spain. Primary outcomes are the efficacy and safety of Icatibant. The main efficacy outcome is the number of patients reaching grades “2” or “1” on the WHO scale within 10 days of starting treatment. Secondary outcomes include “long-term efficacy”: number of patients discharged who do not present COVID-19-related relapse or comorbidity up until 28 days after discharge, and mortality.

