### Objectives {7}

#### Primary objective

The main objective of the ICAT-COVID study is to assess the efficacy and safety of icatibant 10 days after starting treatment (or at hospital discharge if this occurs before) in adult inpatients with SARS-CoV-2 pneumonia and without invasive mechanical ventilation.

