### Trial design {8}

This study is a phase II, randomized, controlled, open-label, proof of concept, multicenter clinical trial with two parallel groups (experimental group: SoC-plus-Icatibant, and control group: SoC) to assess the efficacy and safety of icatibant in patients with COVID-19 pneumonia without invasive mechanical ventilation, and admitted to hospital units. The outcomes of the study protocol are based on the draft master protocol of the WHO for clinical trials that evaluate the efficacy and safety of investigational therapeutics for the treatment of COVID-19 in hospitalized patients (Table 1) [15].

**Table 1 Tab1:** WHO 8-point ordinal scale for clinical status assessment

Patient status	Score
Uninfected: No clinical or virological evidence of infection	**0**
Ambulatory, with no limitation of activities.	**1**
Ambulatory, with limitation of activities.	**2**
Hospitalized, not requiring supplemental oxygen	**3**
Hospitalized, requiring low-flow supplemental oxygen (mask or nasal prongs)	**4**
Hospitalized, on non-invasive ventilation or high-flow oxygen devices.	**5**
Hospitalized, intubated and mechanical ventilation.	**6**
Hospitalized, on invasive mechanical ventilation and additional organ support: extracorporeal membrane oxygenation (ECMO), renal replacement therapy, pressors.	**7**
Death	**8**

Patients enrolled in the study will be randomly assigned at a 1:1 ratio to the experimental group and the control group. The experimental treatment will consist of SoC-plus-Icatibant (3 doses per day for 3 consecutive days (a total of 9 doses). Each dose will consist of 30-mg icatibant administered subcutaneously. The control treatment will consist of SoC only.

Since the beginning of the COVID-19 pandemic, SoC has been mostly supportive, considering the lack of evidence for highly effective therapies. So SoC could vary depending on the scientific evidence available during the study. In this clinical trial (ICAT-COVID), SoC could include respiratory support measures, fluid therapy, antipyretic treatment, postural measures, low-molecular-weight-heparins, corticosteroids such as dexamethasone, remdesivir, and other therapeutic options.

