### Outcomes {12}

#### Primary outcomes

Primary outcomes are the efficacy and safety of icatibant: number (percentage) of patients considered as responders. Responder is defined as a patient who reaches a clinical response [sustained 48-h grade 2, grade 1, or grade 0 classification on the WHO 8-point ordinal scale for clinical status assessment (Table 1)] *and* who has not presented any severe adverse events (grades “3”, “4,” or “5” of the Common Terminology Criteria for Adverse Events -CTCAE- (Table 2)) within 10 days after starting treatment.

**Table 2 Tab2:** Common Terminology Criteria for Adverse Events (CTCAE) Version 4.0

Classification	Magnitude of the adverse event
**Grade 1**	Mild adverse event. Asymptomatic or mild clinical symptoms or just an observation; intervention not indicated.
**Grade 2**	Moderate adverse event. Minimal, local or non-invasive intervention indicated.
**Grade 3**	Serious or medically significant adverse event, but not immediately life-threatening. Hospitalization or hospitalization prolongation indicated; important limitation of self-care.
**Grade 4**	Adverse event with risk of mortality or disability.
**Grade 5**	Death associated with an adverse event.

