*Visits 2* and *3* will correspond to safety assessment during hospital admission. Visit 2 and visit 3 will take place, respectively, on day 2 (24 h after treatment start, before the 4th dose of icatibant) and on day 3 (48 h after treatment start, before the 7th dose of icatibant). *Visit 4* will take place 72 h after treatment start, end of treatment’ visit (after all doses are administered). Hospital discharge may occur after completing visit 4, if the patient is clinically stable (i.e., no fever for 48 consecutive hours without antipyretic medication, PaO_2_/FiO_2_ > 380 or O_2_ saturation > 94%, respiratory rate ≤ 24 bpm, absence of decompensation of any comorbidity).

*Visit 5* [10 (± 1) days after treatment start] will be an efficacy assessment visit. A clinical assessment will be performed and the patient’s clinical status and clinical stability criteria^#^, as well as the medication used and the presence of adverse events, will be reevaluated. If hospital discharge visit overlaps with the day 10 visit, the investigator will only complete the day 10 visit in the e-CRF, clarifying that it is also the hospital discharge visit. The patient will be sent home and will be informed of the confinement regimen measures to be followed at home (or similar, e.g., medicalized hotel), if necessary.

A patient classified as a treatment failure (i.e., non-responder—any patients who do not meet the criteria to be considered a responder) will have their participation in this study terminated. Afterwards, their condition will be treated at the discretion of the physician in charge of their particular case.

^#^Clinical stability (defined as (1) body temperature ≤ 37.5 °C for 48 h without any antipyretic medication, (2) PO_2_/FiO_2_ > 380 or oxygen saturation > 94%, (3) respiratory rate ≤ 24 rpm, and (4) the absence of any kind of comorbidity decompensation) will also be assessed and the time to achieve it will be calculated starting from the time of the baseline visit.

If the patient is discharged before the 10th day since treatment start, the investigator must complete the day 10 visit in the e-CRF for the efficacy assessment on the same day as hospital discharge.

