### Plans to promote participant retention and complete follow-up {18b}

All control visits except the last ONE will be carried out during hospitalization. This last control follow-up visit after hospital discharge will primarily be a phone call interview (carried out by one of the study participant’s physicians). At the evaluating physician’s discretion, a face-to-face medical follow-up visit may be indicated. We expect this straightforward follow-up procedure to encourage participant retention and allow the follow-up process to be properly carried out.

Protocol deviations will be documented and explained in detail by the investigators, and the sponsor will be informed, via the study monitor. In the event of a serious protocol violation, the investigator must inform the sponsor immediately. The monitoring team will record all protocol deviations. The sponsor will review all protocol deviations and assess whether any represent a serious breach according to good clinical practice guidelines. The sponsor will inform the institutional review board (IRB) of any protocol deviations that could impact patient safety and data integrity.

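### The primary endpoint needs 48 h out of hospital, but the efficacy assessment is fixed on the discharge day, so the 48 h is never observed at that assessment

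*Protocol article*

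**What the plan says.** Outcomes {12}, Primary outcomes, defines a responder as a patient who reaches a "sustained 48-h grade 2, grade 1, or grade 0 classification on the WHO 8-point ordinal scale for clinical status assessment" and has no CTCAE grade 3, 4 or 5 event, "within 10 days after starting treatment".

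In Table 1 (Trial design {8}) the worst qualifying grade, 2, is "Ambulatory, with limitation of activities". The next grade, 3, is "Hospitalized, not requiring supplemental oxygen", and grades 4 to 7 are also inpatient states.

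The Primary objective places the assessment "10 days after starting treatment (or at hospital discharge if this occurs before"). Study procedure turns this into an operating rule: for a patient who leaves before day 10, "the investigator must complete the day 10 visit in the e-CRF for the efficacy assessment on the same day as hospital discharge". If discharge falls on the day 10 visit, a single form serves both.

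Daily collection of clinical status is described for the hospital stay. Section {18b} adds: "All control visits except the last ONE will be carried out during hospitalization". That last visit (visit 7) is a call 28 days after discharge. It covers relapses, readmissions, emergency visits, deaths and adverse events, and Table 3 also ticks the clinical status scale for it. Study procedure further states that a patient classed as a non-responder leaves the study.

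The Abstract words the endpoint differently: "The main efficacy outcome is the number of patients reaching grades" 2 or 1 within 10 days, with no 48-h condition.

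**The concern.** The definition asks for two days in a state that begins when the patient leaves hospital, while the assessment is made as the patient leaves. These two rules cannot both be followed for any patient discharged by day 10. Whoever scores the endpoint must either fail these patients, assume the 48 h, or add a later check that the protocol does not describe.

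More than the primary comparison depends on this. Sample size {14} says the results will be used to size a later superiority trial on the same endpoint. The first two secondary outcomes use the same 48-h definition. The interim analysis {21b} counts a patient as complete at discharge if that comes before 10 days, so recent discharges could enter that look before their 48 h have passed.

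**Working it through.** The protocol has no formal sample size calculation, so there is no stated figure to reproduce. The check is one of timing.

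**1. When the 48 h can start.** Grades 1 and 2 are ambulatory and grades 3 to 7 are inpatient. Grade 0 (uninfected) names no setting, but a patient still in hospital with this pneumonia is scored 3 or higher. In practice the 48 h starts at discharge.

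**2. Time accrued at the scheduled assessment.** Time at grade 2 or lower = form date − discharge date.
- Discharge before day 10: the form is dated the day of discharge, so 0 h of 48 h.
- Discharge on day 10: the visits are merged, so 0 h of 48 h.
- Still in hospital on day 10: grade 3 or higher, so not a responder.

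No patient can have been seen to meet the criterion at this assessment.

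**3. Latest discharge that completes 48 h by day 10.** 10 − 2 = day 8. If the ±1 day window of visit 5 were carried into the endpoint, this becomes 9 − 2 = day 7 or 11 − 2 = day 9. Whether a discharge on about day 9 or 10 can count depends on whether the 10-day limit applies to the start or to the completion of the 48 h. The wording allows both.

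**4. Patients involved.** Section {11d} expects about 90% to have a self-limited course within 7–10 days and so to be discharged. It does not say from when those days are counted; I assume treatment start. With N = 120 (Sample size {14}), 0.90 × 120 = 108 patients, or 54 per group. The split over days 7 to 10 is not given, so the range is shown. Readmissions, deaths and grade 3–5 events are ignored.

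| Reading | Discharge days (assumed) | Able to meet the 48-h criterion |
|---|---|---|
| 48 h must have elapsed on the discharge-day form | any | 0 of 120 (0%) |
| 48 h must be complete by day 10 | all on days 7–8 | 108 of 120 (90%) |
| same | even over days 7–10 | 2/4 × 108 = 54 of 120 (45%) |
| same | all on days 9–10 | 0 of 120 (0%) |
| Discharge by day 10 suffices, 48 h assumed or confirmed later | any | 108 of 120 (90%) |

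**5. The adverse event component.** The Outcomes section runs safety assessment from the first dose to 28 (±3) days after discharge. Table 3 ticks adverse event reporting through visit 7, and the visit 7 description agrees. Events between discharge and day 10 are therefore meant to be captured. What is not settled is whether the form completed at discharge already closes this component for patients who leave early.

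**The case against.** The strongest reply is that the endpoint can still be determined. The discharge date is known, and visit 7 collects readmissions, emergency visits and deaths and has the status scale ticked in Table 3. Together these allow 48 h out of hospital to be reconstructed in most cases. This stands, and a reader who infers that the endpoint is unobservable goes too far. What remains is that nothing links visit 7 to the primary endpoint, and the text fixes the efficacy assessment elsewhere. The rule ending participation of non-responders could also remove visit 7 for patients failed on the discharge-day form. That sits badly with section {11b}, which keeps patients who stop early in follow-up for the primary outcome, and with the visit 7 plan itself.

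Two other strong readings are tempting. One is that the adverse event window closes at discharge, so that earlier discharge makes the safety condition easier to meet. The documents do not support this, because event collection continues after discharge and the definition sets 10 days for everyone. The other is that the response rate shifts by a particular number of points. Any single figure needs a discharge-day distribution that the protocol does not give.

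It is also fair to say that the Abstract is a summary. It names safety as a primary outcome alongside efficacy, so its silence on adverse events when describing the main efficacy outcome is unremarkable. Dropping the 48-h condition is still a discrepancy to correct.

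Finally, this is a proof-of-concept trial that disclaims a superiority hypothesis. That lowers the regulatory stakes, but the response rate is the quantity the trial is meant to hand on.

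**Conclusion.** The point holds in a limited form. The primary outcome definition, Table 1, the Primary objective and the discharge-day rule cannot all be followed. At the scheduled assessment the 48-h criterion is met by nobody on observation, so it is either failed by all or assumed. The status of discharges on about days 9–10 is undefined.

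On the protocol's own estimate, about 108 of 120 patients fall under the conflicting rules. If completion by day 10 is required, between 0% and 90% of patients could qualify. That range assumes the 7–10 days run from treatment start and makes no assumption about the spread of discharges within them. It describes what is undetermined and is not an estimate of bias between groups. No sample size figure changes.

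Because this decides how the primary endpoint is scored, it should be settled before the analysis.

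**What to change.** Reconcile the Abstract, the Primary objective, the Primary outcomes definition and Study procedure to one definition. One workable version: grade 2 or lower (discharged) by day 10, no readmission or death in the following 48 h, and no grade 3–5 adverse event through day 10 for every patient regardless of discharge date. This treats the 10-day limit as applying to the start of the response, so a day 10 discharge is confirmed by day 12 (10 + 2).

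Do not finalise responder status on the discharge-day form. Complete it from dated readmission, death and adverse event information, taken from a record or phone check or from dated questions in the existing visit 7 call. Keep patients provisionally scored as non-responders at discharge in that follow-up, and reconcile the rule ending their participation with section {11b} and the visit 7 plan. Apply the same confirmation before a patient counts as complete for the interim analysis.

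The cost is a protocol and e-CRF amendment in an open-label trial with 77 patients already enrolled (Trial status), plus a short check per patient. Earlier patients would need retrospective completion. This may be incomplete, particularly for anyone whose participation was ended as a non-responder. The amendment should be made without reference to results by group, and the number of patients whose 48 h could not be confirmed should be reported.

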### Sample size {14}

No formal sample size estimation was performed. Until now, no clinical trial has been published on efficacy and safety of icatibant in patients infected with SARS-CoV-2. Therefore, previous data on the efficacy of icatibant in patients with SARS-CoV-2 pneumonia to be able to estimate a sample size is not available. Furthermore, the statistical hypothesis of this proof-of-concept trial is not to demonstrate the superiority of “SoC-plus-Icatibant” versus “SoC” in efficacy. Our intention is to include a total of 120 patients (60 in the experimental treatment group and 60 in the control treatment group). The results of this clinical trial will provide information that will allow us to calculate the sample size required for the superiority hypothesis regarding the primary endpoint of the trial, which could be the objective of a future clinical trial.

### Recruitment {15}

The target population of this clinical trial are hospitalized patients diagnosed with SARS-CoV-2 pneumonia who are not on invasive mechanical ventilation (i.e., grades 4 and 5 of the WHO 8-point clinical status assessment ordinal scale—see Table 1). This type of patient usually arrives at the emergency department of each hospital. The investigators of each center will recruit the study subjects prospectively and include them in the study for subsequent randomization at the emergency department if they meet the inclusion criteria and if there is no reason for exclusion (see the “Eligibility criteria {10}” section). The hospitals involved in this clinical trial will avoid participating in other clinical trials that may compete for the same type of patients.

## Assignment of interventions: allocation

### Sequence generation {16a}, concealment mechanism {16b}, and implementation {16c}

Participants will be block randomized using an Internet-based, concealed computer-generated random allocation sequence. Random blocks will be of size 6 and stratified by hospital. The randomized sequence allocation will be stored in the Biostatistics Unit at Biomedical Research Institute of Bellvitge (IDIBELL) and will not be available to any member of the research team. The randomization process will be performed by the investigator using the e-CRF (REDCAP). The randomization list will be computer-generated in blocks of four and stratified for each site. Patients will be assigned to the study groups at the time of enrollment in the study.

## Assignment of interventions: blinding

### Who will be blinded? {17a}

This is an open-label clinical trial; the study medication will not be blinded.

### Procedure for unblinding if needed {17b}

This does not apply because it is an open-label study.

## Data collection and management

### Plans for assessment and collection of outcomes {18a}

Data of interest (see primary and secondary outcomes) will be collected by the study participants’ physicians, who are familiar with this protocol. It will be collected from the anamnesis and from physical examination, which will be recorded in the patients’ digital clinical history, as well as the complementary test information. In both groups, patients will be monitored daily during the first 4 days of hospitalization and the patient’s clinical status and clinical response to treatment will be assessed.

The sponsor will oversee the maintenance of quality control systems while this study is being conducted, using standard operating procedures to do so. Data entry personnel will be given access to the participants’ digital clinical history, so that they can complete the e-CRF.

All trial-related parties accept direct access to the data source, and to the documents and reports related to the study, to be monitored and audited by the sponsor, and for inspection by the regulatory authorities. Source documents of the study must be traceable.

### Plans to promote participant retention and complete follow-up {18b}

All control visits except the last ONE will be carried out during hospitalization. This last control follow-up visit after hospital discharge will primarily be a phone call interview (carried out by one of the study participant’s physicians). At the evaluating physician’s discretion, a face-to-face medical follow-up visit may be indicated. We expect this straightforward follow-up procedure to encourage participant retention and allow the follow-up process to be properly carried out.

Protocol deviations will be documented and explained in detail by the investigators, and the sponsor will be informed, via the study monitor. In the event of a serious protocol violation, the investigator must inform the sponsor immediately. The monitoring team will record all protocol deviations. The sponsor will review all protocol deviations and assess whether any represent a serious breach according to good clinical practice guidelines. The sponsor will inform the institutional review board (IRB) of any protocol deviations that could impact patient safety and data integrity.

### Data management {19}

An electronic case report form (e-CRF) based on REDCap platform (Research Electronic Data Capture software, REDCap Consortium) will be created ad hoc for this study in coordination with the Biostatistics Unit of the IDIBELL (UBiDi). It does not collect data that allows patient identification. Stratification by healthcare center will be implemented when programming the e-CRF. When the computer system assigns the treatment group, therefore, stratification by healthcare center will have already been taken into account.

Data regarding random assignment (date and time), demographic information, clinical history, important clinical complications, clinical data on the acute condition, etiological agent, and hematological and biochemical analysis will be extensively collected, as well as the data regarding the doses of the study treatment administered and of any other treatment.

Adverse events recorded during the study will be coded according to the latest available version of the MedDRA dictionary and described using absolute and relative frequencies by study group, according to severity and relation to treatment. We plan to perform three safety visits during hospitalization (visit 2, visit 3, and visit 4) aimed at collecting possible adverse events, on the first 10 patients recruited. This will allow for safety to be assessed before administering dose 4 and dose 7 of icatibant. If the safety evaluation of the first 10 patients is favorable (i.e., no significant adverse events are observed), the patient recruitment process will continue.

Lastly, the statistician performing the data analysis will be blinded regarding the treatments received by patients (experimental group: SoC-plus-icatibant vs. control group: SoC). R version 3.6.2 or higher for Windows (R Foundation for Statistical Computing) will be used for data processing and analysis.

